### Clinical workflow integration and deployment pathway

After model training and validation, the optimized student model will be integrated into an electronic medical record (EMR)–linked clinical decision-support interface. Routinely available clinical indices will be automatically extracted as model inputs. The system will generate individualized frailty risk scores and intervention suggestions, which will be presented to nephrologists and geriatricians through a structured dashboard. Model outputs will serve as assistive decision-support information, while final clinical decisions will remain under physician supervision, ensuring a human-in-the-loop implementation strategy.

### Validation and evaluation

Internal validation, 70% of data used for model training and 30% for testing within the Chaoyang Hospital dataset. External validation, independent testing using data from six partner centers. Performance metrics, AUC, calibration curve, Brier score, and decision-curve analysis. Model explainability, assessed using SHAP-based feature attribution and causal-effect visualization to ensure interpretability and clinical credibility.

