### Sample size justification

The target sample size is 1,500 participants, based on both prediction-modeling and prevalence-precision considerations. Assuming a frailty prevalence of 20% [3, 7] and approximately 30 candidate predictors, the events-per-variable (EPV) rule (≥ 10) [32, 33] yields the minimum required sample:$$\:n=\frac{10\times\:30}{0.20}=\mathrm{1,500}$$

This ensures adequate frailty events (~ 300) for stable model estimation. Additionally, applying the binomial precision formula for a single proportion,$$\:n=\frac{{z}_{1-\alpha\:/2}^{2}p(1-p)}{{m}^{2}}$$

a total of 1,500 participants provides ± 2% precision (95% CI) around a frailty prevalence of 20%, which is acceptable for multi-center estimation. The chosen size thus satisfies both statistical and practical requirements for developing and externally validating a robust, interpretable prediction model.

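### The 70/30 hold-out within Chaoyang Hospital gives an imprecise internal test and takes 30% of that hospital's frailty events out of model fitting; resampling would avoid both

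*Protocol article*

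**What the plan says.** The Validation and evaluation section of the protocol article describes internal validation as "70% of data used for model training and 30% for testing within the Chaoyang Hospital dataset". It continues: "External validation, independent testing using data from six partner centers". The measures to be reported are listed as "Performance metrics, AUC, calibration curve, Brier score, and decision-curve analysis". The article mentions no resampling. It does not say whether the split is random, temporal or stratified, and it does not say how many participants Chaoyang will contribute.

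The Sample size justification section takes a different starting point. It begins "Assuming a frailty prevalence of 20% [3, 7] and approximately 30 candidate predictors", requires at least 10 events per variable (EPV), and arrives at 1,500 participants. It then concludes: "This ensures adequate frailty events (~ 300) for stable model estimation". No allowance is made there for an internal hold-out or for centres reserved for external testing.

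**The concern.** A hold-out inside the development hospital has two costs. The patients set aside contribute nothing to the fit, and the internal performance estimate rests only on them. Both costs matter when events are limited, and here development is already confined to one of seven centres.

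The six partner centres provide an independent test. The internal step therefore mainly has to show how much performance at Chaoyang is lost to overfitting. Bootstrap optimism correction or repeated cross-validation answers that question with every Chaoyang patient used for both fitting and assessment.

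Two things are at stake. One is the precision of the internal AUC, calibration curve, Brier score and decision curve. The other is the number of events behind a multi-stage model (encoding, factorisation, causal mask, teacher, student) whose student version is meant for a decision-support interface linked to the medical record.

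**Working it through.** **Inputs from the protocol article.** Total 1,500, prevalence 20%, about 30 candidate predictors, EPV of at least 10 (Sample size justification); 70/30 split within Chaoyang (Validation and evaluation); reported prevalence 20% to 50% (Background).

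**Assumptions.** Chaoyang's share s is not stated. I use 30% to 70%, with one seventh (equal centres) as a low case and 100% as an upper bound that cannot occur. The true AUC is taken as 0.75.

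**Step 1: the plan's own figure.** 10 × 30 / 0.20 = 1,500, and 1,500 × 0.20 = 300 events. The stated figure is reproduced, but only with every participant counted as development data.

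**Step 2: events under the stated split.**
- Events in training = 0.70 × 1,500 × s × 0.20 = 210s.
- Events in the internal test set = 0.30 × 1,500 × s × 0.20 = 90s.
- Events if all Chaoyang data are used for fitting = 300s.
- EPV = events / 30.

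**Step 3: precision of the internal AUC.** The Hanley–McNeil variance is [A(1−A) + (n1−1)(Q1−A²) + (n0−1)(Q2−A²)] / (n1·n0), with Q1 = A/(2−A) and Q2 = 2A²/(1+A). For A = 0.75, Q1 = 0.600, Q2 = 0.643 and A² = 0.5625.

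At a half share (45 frail, 180 not frail) the numerator is 0.1875 + 44 × 0.0375 + 179 × 0.0804 ≈ 16.22. Dividing by 8,100 gives 0.00200, so the standard error is 0.0448 and the half-width is 1.96 × 0.0448 = 0.088.

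**Step 4: precision of the calibration slope.** The half-width is 1.96 × √(v/n), where n is the number of test patients and v is the slope element of the inverse logistic information per patient. For a well-calibrated binormal predictor with AUC 0.75 and 20% prevalence, v = 9.24. At n = 225 this gives 1.96 × √(9.24/225) = 0.40.

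| Chaoyang share | Training events (EPV) | Events if all used (EPV) | Test patients / events | AUC half-width | Slope half-width |
|---|---|---|---|---|---|
| 1/7 | 30 (1.0) | 43 (1.4) | 64 / 13 | 0.165 | 0.74 |
| 30% | 63 (2.1) | 90 (3.0) | 135 / 27 | 0.113 | 0.51 |
| 50% | 105 (3.5) | 150 (5.0) | 225 / 45 | 0.088 | 0.40 |
| 70% | 147 (4.9) | 210 (7.0) | 315 / 63 | 0.074 | 0.34 |
| 100% (bound) | 210 (7.0) | 300 (10.0) | 450 / 90 | 0.062 | 0.28 |

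Using all Chaoyang data raises development events by 1/0.7 − 1 = 43% at any share. As a rough guide to the gain in precision, 150 frail and 600 non-frail patients give an AUC half-width of 0.048, against 0.088 for the 30% subset at the same half share.

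**Step 5: sensitivity to prevalence.** At 50%, the top of the range in the Background, a half share gives about 112 test events with AUC half-width 0.064, and a 70% share about 157 events with 0.054. Training EPV is then 262.5/30 = 8.75 and 367.5/30 = 12.25.

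**The case against.** The best defence is that performance assessment does not rest on the internal test set. At a half share and 20% prevalence, the partner centres would supply 750 patients and 150 events, with an AUC half-width of about 0.048. The article ties no decision threshold to the internal AUC. This stands, and it limits the consequence. It does not return the withheld events to the fit.

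Several stronger readings are tempting but are not supported:

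- **That the split is random, so the result depends on the seed and the test set has the same case-mix.** The article names no mechanism. Chaoyang contributes both retrospective and prospective data, so a temporal split is possible. The event counts above hold under any mechanism.
- **That the hold-out serves no purpose.** An internal estimate speaks to overfitting and the partner centres to transportability. If external performance drops, both are needed to explain it. The question is whether a hold-out or resampling supplies the internal estimate more efficiently.
- **That the test set is too small to assess discrimination at all.** Imprecise is the accurate word, and the point weakens if prevalence is near 50% and Chaoyang supplies half or more of the patients.
- **That the smaller training set will visibly damage calibration.** In simulations with 30 predictors, unpenalised logistic regression gave mean slopes of 0.63 at n = 525 and 0.72 at n = 750. Ridge regression gave 1.03 and 1.06, with AUC 0.701 and 0.713. The planned masked network with distillation is neither model, so these figures do not show what it would lose.

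It can also be said that reserving six centres costs more events than the 30% hold-out does. That is true whenever Chaoyang's share is modest: at a half share, 150 events go to the partner centres and 45 to the hold-out. External testing has a value that resampling cannot replace, however, whereas the internal hold-out can be replaced at little cost.

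**Conclusion.** The point holds as one about efficiency and precision. At 20% prevalence and 1,500 participants, the internal test set has 27 to 63 frail patients at Chaoyang shares of 30% to 70%, and at most 90 at any share. For a true AUC of 0.75, the AUC half-width is about 0.113 to 0.074 and the calibration-slope half-width about 0.51 to 0.34. The hold-out removes 30% of Chaoyang's events from fitting.

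At 20% prevalence, training on 70% of Chaoyang falls short of the stated 300 events and EPV of 10 at every possible share. The exact counts depend on the unstated share, and the half-widths on the assumed AUC. Higher prevalence eases both problems: the AUC half-width is about 0.064 at 50% prevalence and a half share.

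A reader might infer that the study cannot establish how well its model performs. The article does not support that, because the six-centre test is separate and may be considerably larger than the internal test set.

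**What to change.** Replace the 70/30 hold-out in Validation and evaluation as follows:

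1. Fit the final model on all Chaoyang participants who have a FRAIL score. The restriction matters because the article lists only demographic, clinical and laboratory data for retrospective cases.
2. Validate internally by bootstrap optimism correction or repeated cross-validation. Each resample should repeat every step: imputation, causal mask, teacher, distillation and student.
3. Report optimism-corrected (or cross-validated) AUC, calibration and Brier score.
4. Lock the model, then test it in the six partner centres as already planned.

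The cost is added computing time, since the whole pipeline is refitted in each resample, plus a change of wording. No extra recruitment is needed, and the article expects recruitment to run to the end of 2027.

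The change does not restore an EPV of 10 at the planning prevalence: at a half share it moves EPV from 3.5 to 5.0. The Sample size justification should therefore give the expected number of Chaoyang participants and the frailty events actually available for model development, instead of citing about 300 events from all seven centres.

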## Background

With population aging accelerating, CKD has emerged as a global health priority, affecting 8–16% of adults and up to nearly 40% of older adults [1, 2]. Frailty, defined as a state of reduced physiological reserve and resilience, is a frequent and severe CKD comorbidity, significantly worsening disability, hospitalization, and mortality [3–6]. Prevalence studies report frailty in 20–50% of older CKD populations [7], driven by metabolic derangements, inflammation, sarcopenia, and multimorbidity [8–10].

Frailty in CKD is clinically important yet potentially reversible [11–13]. Multicomponent interventions combining nutrition, exercise, and psychosocial support have demonstrated benefit, but personalized decision frameworks remain underdeveloped [14–17]. Current screening tools, such as Fried’s phenotype or the FRAIL scale, offer population-level risk estimation but limited mechanistic insight or individualized guidance [18–21].

Artificial-intelligence (AI) methods now offer novel avenues for precision frailty management [22–25], particularly through causal learning and knowledge distillation. However, in routine nephrology practice, non-clinical indices derived from comprehensive geriatric assessment are often unavailable because of resource and workforce constraints, highlighting the need for scalable modeling strategies that can operate under incomplete data conditions. Causal learning disentangles interdependent disease mechanisms, revealing modifiable determinants rather than mere associations [26–28]. Knowledge distillation enables translation from complex multimodal teacher models to lightweight “student” models deployable in clinical settings [29–31]. Applying these methods to CKD-related frailty may bridge data-driven discovery with explainable, clinically actionable models.

This study aims to integrate geriatric assessment with AI-based causal reasoning to (1) identify key frailty-related factors in elderly CKD, (2) develop predictive and interventional-support models using causal learning and model distillation, and (3) evaluate potential real-world clinical feasibility and applicability of the proposed framework.

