### Recruitment and data collection

This is a multicenter, bidirectional cohort study. Eligible participants will be consecutively enrolled from nephrology and internal medicine departments across seven hospitals in Beijing. Retrospective data extraction will be performed only at the coordinating center (Beijing Chaoyang Hospital), while all participating centers will contribute prospective data collection. Pre-admission and admission-related baseline data, including demographic, clinical, and laboratory characteristics, will be retrospectively extracted from the electronic medical records (EMRs) at the coordinating center for eligible historical cases, while baseline standardized assessments will be prospectively performed at hospital admission for newly enrolled participants across all participating centers starting on January 3, 2025. During the prospective data collection phase, each participant will undergo standardized assessments encompassing: structured questionnaires for demographics, comorbidities, physical examinations and anthropometric measurements; laboratory tests including blood and urine biochemistry, inflammatory and metabolic indicators; geriatric assessment scales, frailty, cognition, nutrition, psychological state, physical performance. Collected variables were categorized into two groups: routinely available clinical indices (demographics, medical history, anthropometric measures and laboratory tests) and non-clinical indices, defined as non-routinely acquired geriatric assessment data (frailty scales and cognitive, functional, nutritional, and psychological assessments), which require specialized evaluation and are resource-intensive in routine clinical practice. All data will be entered into a harmonized electronic case-report form (eCRF). The database will be centrally curated at Beijing Chaoyang Hospital, following prespecified data quality control and harmonization procedures described below.

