### Measurements

#### Primary outcome

Frailty status in elderly CKD patients is defined using the FRAIL scale (Fatigue, Resistance, Ambulation, Illness, and Weight Loss; total score ≥ 3 indicating frailty). The primary analytical objective is to examine associations between clinical and non-clinical indices and frailty status and to support the development of individualized frailty risk prediction models.

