### Knowledge-distillation-based model optimization

A teacher–student learning framework will be implemented. The teacher model is trained using full indices including both clinical and non-clinical indices. The student model, restricted to routinely available clinical indices only, is trained by minimizing the distillation loss between teacher and student outputs, enabling the student model to learn compressed representations capturing information patterns related to geriatric assessment and frailty evaluation from routinely available clinical data. This strategy allows simplified deployment of the prediction model in routine clinical environments with limited data availability.

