## Discussion

Frailty in elderly CKD represents a dynamic, modifiable continuum rather than a fixed state [11–13, 34, 35]. Traditional assessments fail to capture individualized causal pathways linking renal dysfunction, inflammation, and functional decline [18–21]. By employing causal learning, this study aims to move beyond purely associative modeling toward improved mechanistic interpretability and clinically meaningful risk stratification [26–28], while knowledge distillation is expected to enhance scalability and applicability of the prediction framework in routine clinical settings with heterogeneous data availability [29–31].

This framework is designed to address real-world heterogeneity in frailty assessment availability across different healthcare settings. Comprehensive geriatric assessment is resource-intensive and not uniformly implemented across hospitals with different service capacities; consequently, many older patients with CKD lack complete geriatric assessment data and are often evaluated using routine clinical indicators only. To address this practical constraint, the proposed teacher–student framework is designed to extend frailty screening and intervention decision-support to data-limited clinical environments. The teacher model leverages comprehensive multimodal data when available, whereas the student model is optimized to operate using routinely collected laboratory and clinical variables. This design enables frailty screening and risk stratification under incomplete data conditions and supports broader applicability across healthcare settings with variable resource availability. In addition, the multicenter study design facilitates model development across heterogeneous CKD populations with different disease severity and comorbidity profiles, further supporting adaptability in diverse clinical environments.

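### With no benchmark in the evaluation, favourable metrics would show that the student predicts FRAIL status, not that it improves on simple use of the same routine data

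*Protocol article*

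**What the plan says.** The Primary outcome section fixes the target: frailty is "defined using the FRAIL scale (Fatigue, Resistance, Ambulation, Illness, and Weight Loss; total score ≥ 3 indicating frailty". The section on knowledge distillation fixes the inputs: "The student model, restricted to routinely available clinical indices only, is trained by minimizing the distillation loss between teacher and student outputs". Outcomes and analysis states that the study is non-interventional and has no follow-up endpoints.

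Validation and evaluation describes a 70/30 split at the coordinating centre and external testing in six partner centres, and then gives the metric list: "Performance metrics, AUC, calibration curve, Brier score, and decision-curve analysis". No comparator model or strategy is named there or elsewhere in the article.

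The rationale is given in the Discussion: "Comprehensive geriatric assessment is resource-intensive and not uniformly implemented across hospitals with different service capacities". The same paragraph adds that many older patients with CKD are therefore often assessed on routine indicators alone. The Background lists FRAIL among existing tools: "Current screening tools, such as Fried’s phenotype or the FRAIL scale, offer population-level risk estimation but limited mechanistic insight or individualized guidance". Aim 3 is to evaluate the framework's potential real-world feasibility and applicability.

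**The concern.** The model is justified by the cost of geriatric assessment, but it is trained for and tested against one short scale, with no later outcome such as disability or death. Every performance figure will therefore describe how well routine data reproduce a FRAIL result.

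That can be useful, but its value depends on a comparison. Where geriatric assessment is lacking, the article says clinicians already use routine indicators. The practical question is whether a causal, distilled network does better than a basic model on those same indicators, and whether distillation itself contributes anything. AUC, calibration, Brier score and a decision curve for the student alone cannot answer either part. If the student clears the default references easily, readers may take that as evidence of applicability and of the framework's merit when it is evidence of neither.

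**Working it through.** **The plan's own figure.** Ten events per variable, 30 candidate predictors and 20% prevalence give n = 10 × 30 / 0.20 = 1,500, with 0.20 × 1,500 = 300 expected frailty events. The 95% half-width is 1.96 × √(0.20 × 0.80 / 1,500) = 0.0202, which agrees with the stated ±2%. The sample size reproduces and is not at issue. The check uses only its prevalence, p = 0.20.

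**Assumptions not in the documents.** The student is perfectly calibrated and follows an equal-variance binormal model, with AUC 0.70 to 0.90 and risk threshold t of 0.10 to 0.30.

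**Formulas.**
- Net benefit: NB = p × sens − (1 − p) × (1 − spec) × t/(1 − t).
- Treat-none: 0. Treat-all: p − (1 − p) × t/(1 − t).
- Student: d = √2 × Φ⁻¹(AUC); cut-off c = [logit(t) − logit(p) + d²/2]/d; sens = 1 − Φ(c − d); spec = Φ(c).

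**Worked case.** For AUC 0.80 and t = 0.20, d = 1.190 and sens = spec = Φ(0.595) = 0.724. Then NB = 0.20 × 0.724 − 0.80 × 0.276 × 0.25 = 0.090.

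| Strategy | NB, t = 0.10 | NB, t = 0.20 | NB, t = 0.30 | Brier |
|---|---|---|---|---|
| Treat-none | 0 | 0 | 0 | – |
| Treat-all | 0.111 | 0.000 | −0.143 | – |
| Student, AUC 0.70 | 0.118 | 0.058 | 0.025 | 0.146 |
| Student, AUC 0.80 | 0.132 | 0.090 | 0.061 | 0.126 |
| Student, AUC 0.90 | 0.154 | 0.127 | 0.107 | 0.092 |
| FRAIL-for-all, no burden charged | 0.200 | 0.200 | 0.200 | 0 |

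Predicting 20% for everyone gives a Brier score of 0.20 × 0.80 = 0.16.

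**How low the default bar is.** At t = p, net benefit reduces to p × (sens + spec − 1), which in this model is above zero whenever AUC exceeds 0.5. Both defaults are then zero. At AUC 0.60, d = √2 × 0.2533 = 0.358, sens = spec = Φ(0.179) = 0.571, and NB = 0.20 × 0.142 = 0.028. A weak but calibrated model already passes, and the student exceeds both defaults in all nine cells above. Clearing the defaults therefore says little about applicability and nothing about distillation.

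**What a FRAIL reference would add.** The last row of the table holds by construction, since FRAIL is scored against itself. It becomes informative only after a burden b per administration is charged, giving 0.200 − b. At t = 0.20 the break-even b is:
- AUC 0.70: 0.200 − 0.058 = 0.142, or one true positive per 7.0 administrations.
- AUC 0.80: 0.200 − 0.090 = 0.110, or one per 9.1.
- AUC 0.90: 0.200 − 0.127 = 0.073, or one per 13.7.

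If the student were used to decide who is asked FRAIL, then at AUC 0.80, per 1,000 patients, the number missed is 200 × 0.276 = 55. The number not asked is 55 + 800 × 0.724 = 634, or about 11.5 administrations avoided per FRAIL-positive patient missed.

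**The case against.** **Stronger readings.** A reader might infer that the student is inferior to current practice because it cannot beat asking FRAIL, or that sites would replace direct screening with a less accurate proxy. The documents support neither.
- FRAIL is not shown to be current practice. Recruitment and data collection places frailty scales among the "non-clinical indices, defined as non-routinely acquired geriatric assessment data (frailty scales and cognitive, functional, nutritional, and psychological assessments", and the Discussion describes practice without geriatric assessment as reliance on routine indicators. The Background names FRAIL as an available tool, not as one in routine nephrology use.
- That no model beats FRAIL when FRAIL is the reference standard is true by construction and is not evidence of a defect. That FRAIL is cheap to ask is an inference from its five components; no administration time or cost is given.
- Replacing direct screening is not a stated use. Outputs are described as assistive and under physician supervision, and the Discussion uses them to identify patients who may benefit from fuller assessment.
- The system is also meant to produce intervention suggestions, so FRAIL-for-all is not a like-for-like alternative to the whole tool.

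These points stand, and they make FRAIL-for-all a secondary reference rather than the main comparator.

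**Level of detail.** An article condenses its methods, and a fuller plan may name benchmarks. The metric list is not wrong as written. But the FRAIL target and the absence of any follow-up outcome are fixed in the text. They limit what these metrics can show, and the conclusions need to respect that whatever the fuller plan contains.

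**The numbers.** They score the student as a stand-alone rule. In a triage pathway, false positives would go on to further assessment, so the gap to 0.200 does not measure harm in the proposed use.

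**Conclusion.** The point holds as a limit on inference. With a FRAIL-defined target, no later outcome and no named benchmark, a favourable AUC and decision curve would show that routine data predict FRAIL status. They would not establish aim 3, or show that the causal and distillation framework improves on basic use of the same data.

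The protocol's sample size and metrics are not in error, and no inferiority to current practice is shown. The net-benefit values of 0.058, 0.090 and 0.127 against 0.200 are illustrative. Prevalence comes from the protocol; AUC, threshold, calibration and the binormal form are assumed. The conclusion that the default references are easy to beat depends on calibration: a student that is miscalibrated in the partner centres could fall below them. This is a cheap and worthwhile improvement.

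**What to change.** In Validation and evaluation, add two benchmarks to the external validation, each assessed on AUC, calibration, Brier score and the decision curve:
1. A prespecified simple routine-data model, such as logistic regression on a few routine variables.
2. The same student trained without distillation, which isolates what distillation contributes.

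Report the differences between the student and each benchmark with confidence intervals.

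As a secondary display, show FRAIL-for-all across a range of explicitly assumed test burdens, since no burden data are listed for collection. At prespecified thresholds, give the FRAIL administrations avoided per FRAIL-positive patient missed.

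Word the conclusion as prediction of FRAIL-positive status where FRAIL has not been administered, not as a substitute for geriatric assessment.

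The two benchmarks use data already being collected and leave the sample size of 1,500 unchanged. The cost is some extra analysis, and the claimed benefit may look smaller.
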